### Expected Outcome

The primary outcome will be to evaluate if existing digital technologies, that is, DSLR camera and smartphone camera are equally efficient as the intraoral scanner for shade selection. The secondary outcome will be to establish a standardized protocol that ensures accuracy and efficiency of tooth shade selection by using readily available, economical digital devices.

### Statistical Analysis

R software (version 4.3; R Foundation for Statistical Computing) will be used to calculate all the results. Descriptive statistics (mean, standard deviation) will be calculated for tooth shade measurements obtained from each method. Intermethod agreement will be evaluated using Bland-Altman plots or intraclass correlation coefficients. Subgroup analyses will be conducted to explore potential factors influencing intermethod agreement (eg, tooth condition, presence of restorations). Sensitivity and specificity analyses will be performed to evaluate the accuracy of smartphone and DSLR cameras compared to that of intraoral scanners by using the latter as the reference standard. Statistical significance will be set at *P*<.05. Additionally, a paired 2-sided *t* test or Wilcoxon signed-rank test will be used to compare the mean shade differences between each pair of methods (intraoral scanner vs smartphone camera, intraoral scanner vs DSLR camera, smartphone camera vs DSLR camera). The effectiveness of a smartphone and DSLR camera in various dental procedures such as examining the existence of restorations or enamel anomalies will be assessed in a subgroup analysis. In this study, we will test statistical assumptions (eg, normality, homoscedasticity) and apply multiple testing corrections (eg, Bonferroni or false discovery rate) to ensure valid inferences. The intraoral scanner will serve as the reference standard for sensitivity and specificity analyses, using ΔE ≤ 2.0 as the threshold for clinically acceptable shade matches.

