### Sample Size

The sample size (N) was calculated using the standard formula:

N = ((Z_α/2_ + Z_β_)^2^ × [P_1_(1 − P_1_) + P_2_(1 − P_2_)]) / (P_2_ − P_1_)^2^

Z_α/2_ = 1.96 for a 95% CI, representing the chosen level of statistical significance; Z_β_ = 0.84, which corresponds to 80% power; N represents the minimum number of samples required per group; and primary variable = reliability percentage.

Based on [12], the reliability of smartphone for classic shade determination = 7.7%, and the reliability of DSLR camera for classic shade determination = 15.4%.

Using a 5% level of significance and 80% power, the sample size calculation is as follows.

N = (1.96 + 0.84)^2^ × [0.077 (1 − 0.077) + 0.154 (1 − 0.154)] / (0.154 − 0.077)^2^

This yields a minimum required sample size of 221 participants per group.

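### The stated 80% power is set at an unadjusted 5% level for one device pair, with no allowance for the multiple testing correction planned for the analysis

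*Protocol article*

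**What the plan says.** In the protocol article, the Sample Size section fixes the level and power as "Z_α/2_ = 1.96 for a 95% CI, representing the chosen level of statistical significance" and "Z_β_ = 0.84, which corresponds to 80% power". It sizes the study on one binary quantity ("primary variable = reliability percentage") and one pair of devices, with planning values "the reliability of smartphone for classic shade determination = 7.7" per cent and "the reliability of DSLR camera for classic shade determination = 15.4" per cent. The calculation is introduced with "Using a 5% level of significance and 80% power, the sample size calculation is as follows", and the result is given as 221 per group.

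The Statistical Analysis section sets significance at 0.05 and states that a paired t test or Wilcoxon signed-rank test "will be used to compare the mean shade differences between each pair of methods". It lists three pairs: scanner v smartphone, scanner v DSLR, and smartphone v DSLR. It then commits the study to "apply multiple testing corrections (eg, Bonferroni or false discovery rate", given as examples. It does not say which tests form the corrected family or which method will be used.

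The Expected Outcome section makes the primary question each camera against the scanner. The Data Collection Procedure section has every participant measured with all three devices.

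**The concern.** Power belongs to a particular test at a particular level. The article plans at 5% for one comparison, but announces an analysis in which a comparison may have to pass a stricter threshold. If the three device pairs are the corrected family, the level used for planning is not the level used for analysis, and the printed 80% describes a test that will not be carried out in that form.

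This matters here because the study hopes to find the cameras as good as the scanner. With tests of difference, lower power makes a non-significant result more likely, and an overstated 80% would make such a result look more reassuring than it is. Inferring equality from non-significance is a separate weakness, which correcting the power statement would not cure.

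**Working it through.** **Inputs, all from Sample Size unless noted.** P1 = 0.077 (smartphone), P2 = 0.154 (DSLR), Zα/2 = 1.96, Zβ = 0.84, stated N = 221 per group. Number of pairs = 3 (Statistical Analysis).

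**Step 1: reproduce the stated figure.** With the printed formula:

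- Variance term v = 0.077 × 0.923 + 0.154 × 0.846 = 0.0711 + 0.1303 = 0.2014.
- N = (1.96 + 0.84)² × 0.2014 / 0.077² = 7.84 × 0.2014 / 0.005929 ≈ 266.3, so 267.

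The stated 221 is not reproduced. That is a separate error. It is kept apart below by showing both sample sizes.

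**Step 2: the level after correction.** Bonferroni over three pairs (assumed family) gives 0.05/3 = 0.0167 two-sided, Z = 2.394. Over only the two scanner comparisons it gives 0.025, Z = 2.241.

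**Step 3: power under the article's own independent-proportions formula.** Power = Φ(0.077/√(v/N) − Z).

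- N = 267: √(0.2014/267) = 0.0275, and 0.077/SE = 2.80.
- N = 221: √(0.2014/221) = 0.0302, and 0.077/SE = 2.55.

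| Level | N = 267 | N = 221 |
|---|---|---|
| 0.05 (no correction) | 80% | 72% |
| 0.025 (Bonferroni, two tests) | 71% | 62% |
| 0.0167 (Bonferroni, three tests) | 66% | 56% |

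The correction over three pairs alone costs about 14 points at 267 (80 − 66) or 16 points at 221 (72 − 56). The arithmetic error alone costs about 8 (80 − 72).

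For 80% power at 0.0167 the formula needs (2.394 + 0.842)² × 0.2014 / 0.005929 ≈ 355.5, so 356. This is given only to show the size of the gap.

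**Step 4: false discovery rate control.** With Benjamini-Hochberg over three tests, the effective level for one pair lies between 0.0167 and 0.05. Power is then between about 56% and 72% at 221, and between about 66% and 80% at 267. The upper end applies only when both other pairs are also significant at 5%.

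**Step 5: allow for pairing.** For a McNemar-type comparison with within-person correlation φ (not given in the article; assumed here):

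- Discordant proportion ψ = P1(1 − P2) + P2(1 − P1) − 2φ√[P1(1 − P1)P2(1 − P2)] = 0.2073 − 2φ × 0.0962.
- Power = Φ{[0.077√N − Z√ψ] / √(ψ − 0.077²)}.

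| φ (assumed) | ψ | Power at 0.05, N = 221 | Power at 0.0167, N = 221 |
|---|---|---|---|
| 0 | 0.207 | 71% | 55% |
| 0.3 | 0.150 | 85% | 72% |
| 0.5 | 0.111 | 94% | 86% |

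Power reaches 80% at 0.0167 when φ is about 0.42.

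**Step 6: the tests actually listed.** The paired t or Wilcoxon tests compare mean shade differences. The article gives neither an effect size nor a standard deviation for these, so their power cannot be computed at any level.

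**The case against.** There are four serious counter-arguments.

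- **The family is not stated.** The correction sentence follows directly on one about subgroups and names neither family nor method. Those choices are commonly left to a statistical analysis plan, which is not shown. This stands: Bonferroni over three pairs is an assumption, and the missing choice is not itself the fault. If the correction covered only subgroups, the pairwise tests would stay at 5% and the article would need only to say so. However, the three pairs are the only hypothesis tests listed one by one, and any correction that includes them leaves the article's formula short of 80%.
- **The design is paired.** This also stands, and it is why the point is not put more strongly. The article sizes the study with an independent-groups formula and states no correlation, so it cannot claim the gain, but a correlation of about 0.42 or more would bring 221 participants to 80% even at 0.0167.
- **The 56% is not the power of any listed test.** Correct. It is the article's own power statement carried to a stricter level. That the listed tests have no computable power does not rescue the 80%.
- **The 56% mixes two errors.** Correct. The effect of the correction alone is the fall from 80% to 66% at 267.

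A reader might therefore infer that the study definitely lacks 80% power, or that its true power is 56%. The documents support neither statement. The first ignores pairing. The second depends on an assumed family and method, on the separate 221 v 267 error, and on a test the analysis section does not list.

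**Conclusion.** The point holds in a limited form. The article's 80% refers to one unadjusted 5% comparison, while the analysis plans three pairwise comparisons and a correction for which the sample size makes no allowance. The stated power does not carry over to a corrected test.

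If the family is the three pairs, the correction takes power under the printed formula from 80% to about 66% at 267 with Bonferroni, and from about 72% to about 56% at 221, with smaller losses under false discovery rate control. Once pairing is allowed for, the range at 221 and 0.0167 straddles 80%. The claim is unsupported as written, and it is not shown to be false. Correcting 221 to 267 would not settle it, because that restores 80% only for an uncorrected test.

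**What to change.** No participants need be added. Choose one of two routes, after the sample size arithmetic has been put right:

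1. **Protect the primary comparisons.** Pre-name them in line with Expected Outcome (each camera v the scanner), test them in a fixed order at 5%, and correct only the remaining tests. State power for that primary comparison. The Sample Size section gives planning values for the smartphone and DSLR only, so one for the scanner, or an effect size and standard deviation for the paired shade difference, must be supplied.
2. **Keep the correction over all three pairs.** State the family and the method, and restate power at the corrected level for the planned paired test, with the assumed correlation shown. Quoting 56% would only replace one independent-groups figure with another.

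The cost is a few sentences in Sample Size and Statistical Analysis. The Results section says that no one has been recruited, so the change can be made before any data exist. The drawback is that the stated power may become less favourable.

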## Results

This study was intramurally funded in December 2024. Data collection is scheduled to commence following the publication of this study protocol. As of submission, no participants have been recruited, and data analysis is yet to begin. Results are expected to be completed and published in early January 2026.

## Discussion

A smartphone, DSLR camera, and intraoral scanner will be used to capture and match the shade of a patient's teeth. The smartphone offers a simple portable tool for basic shade reference, while the DSLR camera provides high-quality, controlled images for accurate shade matching under standardized lighting. The intraoral scanner creates a detailed 3D map of the teeth, enabling precise, customized shade selection that can be compared with physical shade guides for optimal restoration outcomes. Advancements in digital dentistry, such as colorimeters, intraoral scanners, and computer-aided shade matching systems, have significantly transformed the shade selection process [13]. These technologies have greatly improved treatment outcomes and patient satisfaction by offering greater accuracy, efficacy, and consistency in shade matching. This study focuses on evaluating the efficiency of smartphone cameras and DSLR cameras in the field of tooth shade selection. Our research seeks to determine their utility as alternatives to subjective methods and cost-intensive objective method for shade selection in dentistry. A study conducted by Yung et al [14] compared the color consistency of digital images captured in a clinical setting by using smartphone cameras and single-lens reflex (SLR) cameras. They found that color accuracy is not considerably increased by using a polarizer. An effective substitute would be a smartphone camera that has an external light source attached to it.

Ziadeh et al [15] assessed the repeatability of the intraoral scanner for selecting dental shades in the anterior and posterior regions. They found that the intraoral scanner demonstrated better repeatability in the anterior region when compared to the visual method, and the difference between the two approaches is clinically acceptable. Faezeh et al [12] examined the validity of color selection techniques by using visual assessments, intraoral scanning, and photography (using an SLR camera and a smartphone). By evaluating and contrasting the dependability of the 3 most popular methods of color selection, that is, visual assessment, intraoral scanning, and photography, oral scanners showed more accurate results.

Abu-Hossin et al [16] compared the use of digital techniques for visual shade selection and evaluated the intraoral scanners' reproducibility. They found that while intraoral scanners are a useful addition for color determination, the visual approach should also be used for confirmation. Moussa et al [17] evaluated the measurements in photos taken with a DSLR, intraoral scanner, and smartphone camera at various distances. According to their study, the measurements of the maxillary right incisors using an intraoral scanner, DSLR, and smartphone (at a minimum distance of 24 cm) did not differ. Both the intraoral scanner and the visual method showed color differences in the central and canine regions that were below the perceptibility threshold—implying that the differences were so small that they could not be noticed by the human eye; these findings are consistent with the investigation performed by Mehl et al [18]. Ebeid et al [19] examined 3 intraoral scanners, namely, CEREC Omnicam (Dentsply Sirona), CEREC Primescan, and 3Shape Trio (Copenhagen, Denmark) by using the Vita Easyshade V spectrophotometer as the control. Ten distinct shades of Vita Mark II blocks were employed in the investigation. Each piece of equipment measured 10 colors per specimen by using the Vitapan Classical shading technique. The accuracy and repeatability data were obtained. According to their study, the accuracy and repeatability of all the intraoral scanners fell short of expectations. Therefore, the authors recommended using the color detection capability of the intraoral scanners with caution. Rutkunas et al [20] compared the accuracy of the intraoral digital 13 scanner, 3Shape Trios, with that of a spectrophotometer, SpectroShade, as a control, and they found that the Trios' mean accuracy for the Vitapan Classical shade tabs was just 27.5%, whereas that for the Vitapan 3D Master shade tabs was 53.3%. Fattouh et al [21], Gasparik et al [22], and Moussaoui et al [23] compared the accuracy, repeatability, and reproducibility of digital intraoral scanners for shade selection and verified whether intraoral optical scanning devices can be used to determine the color of restorations without requiring additional conventional color-measurement methods and concluded that the intraoral scanner Trios color could be an alternative to other methods for shade selection. Czigola et al [24] evaluated the shade measurement function of a digital scanning system (3Shape Trios 3) in relation to visual shade determination (Vita Classical and Vita Linearguide) and a digital spectrophotometry device (Vita Easyshade). Intraoral scanners proved to be as accurate as spectrophotometers; they could serve as objective and time-efficient tools for shade selection and could be seamlessly integrated into comprehensive patient case documentation, as reported by Vitai et al [25]. Although previous research has compared the accuracy of intraoral scanners and smartphone cameras, our study expands the scope by evaluating all 3 digital technologies together by comparing the smartphone camera, DSLR camera, and intraoral scanner to determine how each performs in tooth shade selection. This allows for a more comprehensive assessment of their relative accuracy and clinical usefulness. This study is an attempt to confirm the use of digital technologies for shade selection; if we obtain positive results, further research is warranted to ascertain its universal applicability.

When comparing the reliability of AI-assisted technologies such as intraoral scanners to that of DSLR and smartphone cameras, it is commonly anticipated that intraoral scanners will exhibit higher reliability. Intraoral scanners are specifically designed for dental applications, providing detailed and accurate images of intraoral structures, including teeth. Their direct intraoral capture minimizes the potential sources of error such as variations in lighting or camera positioning, which can affect the reliability of images obtained by DSLR and smartphone cameras. Additionally, intraoral scanners often incorporate advanced technology and software algorithms tailored for precise shade matching and analysis, further enhancing their reliability in dental practice. Therefore, in the context of tooth shade evaluation, it is expected that intraoral scanners will generally offer higher reliability compared to DSLR and smartphone cameras.

## Abbreviations

AI: artificial intelligence
DSLR: digital single-lens reflex
SLR: single-lens reflex
